### Aim 3: Test the Prototype for Better Comprehension and Adherence to Medication Information

Our hypothesis for this aim is that the AI-powered visualization tool in the app improves medication information comprehension and adherence when compared with written medication information and contextual plain-text information.

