#### Study Design

The study has a single-blind and sequentially randomized design. The full design of the study will include two arms with 2 (modality: app versus app with text) × 2 (format: an app with visualization versus an app with contextual medication text information) × 2 (context: contextual medication information versus information without context) + 1 (control: app) design. The design is depicted in Figure 1. The randomized trial using binary options (*yes* or *no*) provides the stratification needed to identify groups that are prone to get benefits from the different presentations of medication information. The results from the sequential randomized design will help us detect statistically significant differences using a larger sample size. The first randomization helps with filtering patients who have better information recall regardless of the app. The second randomization helps with finding the actual effects of the tool when compared with different interventions.

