#### Procedure

In the first randomization, patients will be randomized into two groups at baseline. The control group (ie, the app-only [A] group) will have the smartphone app with no visualization, and the intervention group will have the app with text information only as in the current Medication Guide (AT) [43]. At 4 weeks, patients from both the control and intervention groups from both arms, who have scores of 80% or higher in the information recall survey, will continue in the study with the same intervention, in either the A or AT group. Those who do not meet the performance cutoff will be rerandomized further into two groups for each arm. In the second randomization at 4 weeks, the control group from the first arm (A) will have the smartphone app with just text information about medication (AT), and the intervention group will have the smartphone app with the prototype of medication information visualization (AV). The control group from the second arm (AT) will have the app with contextual medication information in a text format (ACT), and the intervention group will have the app with our visualization design (AV). This part of the study will continue for 8 weeks. The monitoring is not a continuous process. Only the principal investigator will have access to the main file and will check the adherence and patient analytics at 4 and 8 weeks.

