#### Sample Size Justifications

To detect a 1-point improvement on the Likert scale and 80% power at the 5% significance level, the study would require 100 subjects in each group with 1:1 allocation for the second randomization (ie, AT: AV and ACT: AV). To allow for an 11% loss due to dropouts and those lost to follow-up, we would need to recruit 888 patients, allowing up to 50% of the patients to move to the second randomization following the first randomization with a score of 80% or higher in the medication recall questionnaire survey with assigned intervention. Recruitment of 888 patients is also sufficient to detect a 1-point improvement on the MMAS-8 (the secondary outcome), with 80% power at 5% significance. Therefore, our target is to recruit 900 patients.

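### Visualization is compared only among patients below 80% recall at week 4, at most about 100 versus 100 per contrast, so the larger-sample rationale does not apply to it and the Aim 3 hypothesis is too wide

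*Protocol article*

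**What the plan says.** The opening of Aim 3 gives one hypothesis: the visualization tool "improves medication information comprehension and adherence when compared with written medication information and contextual plain-text information". It names two comparators and sets no limit on the patients by recall.

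The Study Design section justifies the two-stage scheme: "The results from the sequential randomized design will help us detect statistically significant differences using a larger sample size". It then explains that the first stage filters out patients who recall well anyway, and that the second stage shows what the tool itself does.

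The Procedure section fixes the flow. Everyone starts on the app alone (A) or the app with Medication Guide text (AT). At 4 weeks, patients at 80% recall or above stay on what they have. For the others: "Those who do not meet the performance cutoff will be rerandomized further into two groups for each arm". From A the options are AT or AV. From AT they are contextual text (ACT) or AV.

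The Aim 3 Sample Size Justifications section plans the second stage for a one-point Likert gain, with power of 80% and a 5% level: "the study would require 100 subjects in each group with 1:1 allocation for the second randomization". The two comparisons it names are AT:AV and ACT:AV. After an allowance of 11% for losses it arrives at 888 to be recruited. That total rests on a further assumption, namely "allowing up to 50% of the patients to move to the second randomization following the first randomization". The recruitment target is then set at 900.

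**The concern.** A two-stage scheme that withholds visualization from good recallers, and then splits the remaining patients over two separate contrasts, leaves fewer patients for the visualization question than the trial enrols. The stated rationale suggests a gain in sample size. For this question there is a loss.

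The population is affected as well. Patients at or above the cutoff never receive AV, so no randomized comparison says anything about AV in them. The hypothesis does not carry that limit. A positive result could then be reported as visualization being better than written information for users of the app in general, when it was shown only in patients selected by their week-4 recall.

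**Working it through.** **Inputs (Aim 3 Sample Size Justifications):** 100 per second-stage group; two 1:1 contrasts, so four groups; up to 50% rerandomized; 11% loss; 888 recruited, target 900; 80% power; 5% significance. Sidedness is not stated, so two-sided is assumed. No SD is given.

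**1. Reproduce the plan's figure.**
- Rerandomized: 4 × 100 = 400.
- Evaluable: 400 / 0.50 = 800.
- Recruited: 800 × 1.11 = 888, as stated. Dividing by 0.89 instead gives 899, which the target of 900 covers.

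**2. Patients in each AV contrast**, assuming the two first-stage arms send equal shares to the second stage.
- Each contrast: 100 + 100 = 200 of 800, or 25%.
- Both contrasts: 400 of 800, or 50%. The other 400 are in no AV comparison.
- From 888 recruited: 888 × 0.89 = 790; 790 × 0.50 / 4 ≈ 99 per group.
- From 900 recruited: 900 × 0.89 = 801; 801 × 0.50 / 4 ≈ 100 per group.
- The plan's share is a ceiling (up to 50%). So 100 per group is the planned maximum, and at least half of patients lie outside the AV contrasts.

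**3. Detectable difference in SD units:** d = (1.96 + 0.84) × √(2/n).

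| Layout of 800 evaluable patients | n per group | d |
|---|---|---|
| Each AV contrast as planned | 100 | 0.40 |
| Single-stage, three groups (AV, AT, ACT) | about 266 | 0.24 |

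The ratio is √(266/100) ≈ 1.6. A 1-point difference detectable with 100 per group implies an SD of about 1/0.397 ≈ 2.52. On that SD the two rows are 1.00 and 0.61 point. The comparison assumes the same effect and SD in all patients and the same unadjusted 5% level.

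**4. If fewer than 50% are rerandomized** (illustrative shares, 1 point, SD 2.52):
- 40%: 800 × 0.40 / 4 = 80 per group, power about 71%.
- 30%: 800 × 0.30 / 4 = 60 per group, power about 58%.

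**5. Who is in the contrasts.** The Procedure rerandomizes patients who miss the 80% cutoff. The Sample Size Justifications section runs on from its 50% allowance to a score of 80% or higher, and can be read as sending the high scorers to the second stage. The two sections need reconciling. On either reading AV is tested only in a subset selected on week-4 recall, and the count of 200 of 800 is unchanged. The description of that subset as below 80% rests on the Procedure.

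**The case against.** The strongest reply is that nothing is hidden. The Study Design section openly describes the filtering, the Procedure states the rule in full, and the sample size is built for it. Testing a tool in patients who did poorly without it is a legitimate choice. All of that stands, and the point does not ask for another design. But disclosure of the filter makes the unrestricted hypothesis inconsistent with the document's own scheme.

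The sample-size sentence also names no comparator. A reader might infer that it flatly contradicts the design. The text does not support that, because it may mean only that the whole trial is large, as the Aim 3 Limitations section says of enrolment. What can be said is that the sentence is untrue of the visualization comparison, the only hypothesis stated for this aim.

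Two further readings go too far:
- A reader might infer that the scheme doubles the smallest detectable effect, by setting 0.40 SD against about 0.20 SD for one comparison of 400 versus 400. The hypothesis names two comparators, so a single-stage trial needs at least three groups, and the ratio is about 1.6. Even that assumes the same effect in everyone. Patients already at 80% have less room to improve on recall, and including them could dilute the effect.
- A reader might infer that the published conclusions overclaim for AV. Neither the abstract's conclusions nor the closing Conclusions section compares AV with text. Only the Aim 3 hypothesis lacks the limit.

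Pooling the two AV groups does not remove the point. The plan sizes the contrasts separately, and pooling would still cover only the 400 rerandomized patients. High scorers can still be compared between A and AT; they are absent only from the AV contrasts.

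**Conclusion.** The point holds in this limited form. Each AV contrast is planned on at most about 100 versus 100 of about 800 evaluable patients, and at least half of patients are in neither. The sequential step therefore does not give the visualization comparison a larger sample. Against a three-group single-stage benchmark, the detectable difference is about 1.6 times as large (0.40 versus 0.24 SD), assuming two-sided 5%, 80% power, equal shares from both arms, and a common effect and SD.

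The hypothesis is wider than the randomized evidence, which concerns only patients selected by week-4 recall, separately within each first-stage arm. The planned power for 100 per group is not challenged. The correction is worth making because it changes what the trial may conclude.

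**What to change.** 1. **Study Design:** delete the sentence on a larger sample size, or say which comparison it refers to.
2. **Sample Size Justifications:** state that each AV contrast is planned at about 100 versus 100 and will be smaller if fewer than 50% of patients are rerandomized.
3. **Aim 3 hypothesis, and any AV conclusion drawn from it:** restrict to patients scoring below 80% on recall after 4 weeks on A (AV versus AT) or on AT (AV versus ACT). Make no AV claim for patients at or above the cutoff.
4. **Sample Size Justifications and Procedure:** reconcile the wording on which patients go to the second randomization.

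The cost is wording only, with no extra patients and no change to allocation. The downside is a narrower, less favourable claim for the tool.

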**Figure 1 figure1:**
[figure not shown]
Study design. The participants are randomized first at R: one group uses only the app (A) and another group is given the app with medication information text (AT). At time point 1 (T1), after 4 weeks, both groups are evaluated for information recall (>80%). Then, after a second randomization (R), the participants are divided into the following groups: app with medication information text (AT), app with contextual medication information text (ACT), and app with visualization (AV). T0: baseline; T2: time point 2 (after 12 weeks).

#### Intervention

The study will include three intervention conditions loaded into the smartphone app platform. We can better compare the effects of the medication information visualization tool by comparing the outcomes of these three interventions to understand the impacts of our visualization. In the first condition, the app with medication information text (AT), the medication text information will be loaded into the app platform. This medication text is the Medication Guide, which is approved by the FDA. In the second condition, the app with contextual medication information text (ACT) is shown as a printed-text version. This contextual information (ie, 10 pieces of crucial information patients should know) that we included in our visualization will be shown only as the text version in this intervention. In the third condition, an app with visualization (AV), the interactive app will be loaded with our medication information visualization tool, including the visual format of the contextual information.

#### Study Subjects and Recruitment Methods

We will recruit patients (18-65 years of age) from our clinics. Inclusion criteria will include participants who have access to a smartphone, can provide their consent, do not have any cognitive impairment, and who have at least two medications on profile for which we have created a visualization. At the time of recruitment, we will ensure that the patients meet the minimum cutoff score of 34 during cognitive screening using the TICS-M test and health literacy level [32]. Eligible patients will be allocated in a 1:1 ratio to the two arms of the study according to a computer-generated random sequence stratified by third-party software.

#### Procedure

In the first randomization, patients will be randomized into two groups at baseline. The control group (ie, the app-only [A] group) will have the smartphone app with no visualization, and the intervention group will have the app with text information only as in the current Medication Guide (AT) [43]. At 4 weeks, patients from both the control and intervention groups from both arms, who have scores of 80% or higher in the information recall survey, will continue in the study with the same intervention, in either the A or AT group. Those who do not meet the performance cutoff will be rerandomized further into two groups for each arm. In the second randomization at 4 weeks, the control group from the first arm (A) will have the smartphone app with just text information about medication (AT), and the intervention group will have the smartphone app with the prototype of medication information visualization (AV). The control group from the second arm (AT) will have the app with contextual medication information in a text format (ACT), and the intervention group will have the app with our visualization design (AV). This part of the study will continue for 8 weeks. The monitoring is not a continuous process. Only the principal investigator will have access to the main file and will check the adherence and patient analytics at 4 and 8 weeks.

#### Survey Tools

Three survey measures will be used. The first survey will be used to understand information recall; we will design a timed questionnaire, with *true* or *false* responses, for each medication in a patient’s regimen that includes the 10 pieces of crucial medication information we embedded into the visualization interface. Each patient will be tested on different medications at 4 and 12 weeks to show understanding and knowledge. For example, if a patient takes simvastatin, metformin, and losartan, only those specific medication-related questions will be asked. The second survey will help us to understand the patient’s perception of medication knowledge. We will use a validated survey instrument to assess patients’ attitudes, confidence, and perceived medication knowledge [44]. This instrument was validated with high internal consistency (Cronbach α=.833). The third survey will use the 8-item Morisky Medication Adherence Scale (MMAS-8). The MMAS-8, whose scores range from 0 to 8 with lower scores indicating lower adherence, is a widely used tool for self-reported medication adherence; the scale was found to be reliable and significantly associated with adherence control (*P*<.05), with 93% sensitivity as well as 53% specificity for low adherence in a validation study [37].

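### Survey Tools contradicts itself on which medications are tested for recall at each visit; read literally, the week-4 cut-off score and the 12-week recall subscale cover different drugs

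*Protocol article*

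**What the plan says.** Three consecutive statements in the Aim 3 Survey Tools section bear on the content of the recall test.

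- The timed true/false questionnaire is designed "for each medication in a patient’s regimen that includes the 10 pieces of crucial medication information we embedded into the visualization interface".
- Next: "Each patient will be tested on different medications at 4 and 12 weeks to show understanding and knowledge".
- Then an example: "if a patient takes simvastatin, metformin, and losartan, only those specific medication-related questions will be asked".

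The Aim 3 recruitment section admits patients "who have at least two medications on profile for which we have created a visualization", so two is the minimum. Under Procedure, patients "who have scores of 80% or higher in the information recall survey, will continue in the study with the same intervention", and those below the cut-off are re-randomized. Study Measures makes the primary outcome a composite of three subscales, of which recall is one. Data Collection sets the primary time point at 12 weeks and lists only demographics at baseline. Data Analysis names t tests, chi-square tests and univariate analysis of variance, with general linear modeling if the data are not normal. It mentions neither a change score nor adjustment for the week-4 score.

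**The concern.** If the questionnaire covers every drug in the regimen, no drug is left to be different at week 12 unless the regimen changes. The second statement has each patient as its subject and ties the difference to the two visits, so its literal meaning is a change of drugs within the patient. Nothing in the article says which drugs are tested when.

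The week-4 score matters for two reasons. It decides who enters the second randomization, where the app with visualization (AV) is compared with the Medication Guide text (AT) or the contextual text (ACT). It is also the only recall measurement scheduled before that randomization, so it is the only such score available for adjustment. If drugs are switched, a patient may be kept out of re-randomization because of good recall of one drug while recall of the other, tested later, is poor. Patients who pass by chance stay on their first allocation and are lost to the AT:AV and ACT:AV comparisons.

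**Working it through.** **The plan's own figure.** Four second-stage groups of 100 with 50% moving on gives 4 × 100 / 0.50 = 800. Adding 11% gives 800 × 1.11 = 888, as stated. Dividing by 0.89 instead gives 899, still below the target of 900. This figure rests on one Likert point, not on recall, so the present point does not change it.

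**Effect of test length on the cut-off.** Inputs from the article are at least two medications, 10 pieces of information per medication, true/false scoring and a pass mark of 80% or higher. Assumptions that the article does not give:

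- one item per piece of information;
- independent items with one true recall probability p per patient;
- for the literal reading, one drug per visit for a two-drug patient.

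The test then has 10 items (pass at 8) if the drugs are split across visits, and 20 items (pass at 16) if both are tested each time. The chance of passing is P(X ≥ 8) for X ~ Bin(10, p), or P(X ≥ 16) for X ~ Bin(20, p):

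| True recall p | 10 items | 20 items |
|---|---|---|
| 0.50 (pure guessing) | 5.5% | 0.6% |
| 0.60 | 16.7% | 5.1% |
| 0.70 | 38.3% | 23.8% |
| 0.75 | 52.6% | 41.5% |
| 0.80 | 67.8% | 63.0% |
| 0.90 | 93.0% | 95.7% |

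The standard error of one patient's score is √(p(1 − p)/k). At p = 0.80 it is √(0.16/10) = 12.6 points on 10 items and √(0.16/20) = 8.9 points on 20.

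**Effect of test length on the week-4 score as a covariate.** Assume mean recall 0.70 and a between-patient SD s of true recall. The reliability of a k-item score is s² / (s² + (0.21 − s²)/k). On 10 versus 20 items this gives:

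- s = 0.05: 0.11 versus 0.19
- s = 0.10: 0.33 versus 0.50
- s = 0.15: 0.55 versus 0.71
- s = 0.20: 0.70 versus 0.83

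This covers length only. Different drug content at week 12 could lower the correlation further.

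**Gain from adjustment.** Adjusting for a score with correlation r leaves a share 1 − r² of the variance. For assumed r of 0.2, 0.4 and 0.6 the reduction is 4%, 16% and 36%. The article gives no r. Everyone re-randomized scored below the cut-off, and that restricted range would usually lower r.

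**The case against.** The best counter-argument is the example. It names three drugs together, shows no split by visit, and illustrates that patients are asked only about their own drugs. The disputed sentence may therefore have been meant to say that medications differ between patients. That is possible, and it is why this is a contradiction to resolve and not a settled design error. The sentence would still need rewording, because sites following it as written would give a different test.

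Stronger conclusions that a reader might draw are not supported:

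- **That the test is shortened or halved.** The article gives no item count per visit and no rule assigning drugs to visits. Halving applies only to a two-drug patient tested on one drug per visit; the article's own example has three drugs.
- **That the whole primary outcome is affected.** Only the recall subscale is.
- **That the 12-week comparison is biased.** Re-randomized groups would have their test drugs chosen in the same way, and entry depends on the observed score in every group. The cost is noise, and a change in who enters.
- **That a planned change score is spoiled.** None is planned.
- **That the loss of precision has a known size.** Any figure depends on correlations with no source in the article.

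It is also fair to say that new content at week 12 limits memorizing of tested items. Reworded items on the same drugs also serve that purpose. A further objection stands in part: the practice effect need not be equal across groups, because patients keep different app content for 8 weeks and can look up what they were asked.

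**Conclusion.** The point holds as a contradiction in the Survey Tools section with a moderate statistical cost if the disputed sentence is followed literally. The week-4 sorting score and the 12-week recall subscale would then cover different drugs, and a two-drug patient could be tested on one drug per visit.

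Under the stated assumptions, the chance of wrongly passing rises by 11.6 percentage points at true recall 0.60 (16.7 − 5.1) and by 14.5 at 0.70 (38.3 − 23.8). At 0.80 the two tests differ by 4.8 points (67.8 − 63.0), and at 0.90 the shorter test fails slightly more patients. Randomized comparisons remain valid, and the recruitment figure of 888 is untouched. The benefit of adjusting for the week-4 score is real in principle but cannot be sized from the article.

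**What to change.** Replace the disputed sentence with a statement that, at both 4 and 12 weeks, each patient is tested on every medication in the regimen that has a visualization, using parallel reworded true/false items at week 12. In Data Analysis, state that the 12-week recall score is compared between the re-randomized groups (AT versus AV, and ACT versus AV) with adjustment for the week-4 recall score.

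While editing, align the threshold. Procedure uses 80% or higher, whereas the Figure 1 legend shows a strict inequality. On a 10-item test, 8 correct is exactly 80%, so the two versions sort that patient differently.

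The cost is a few sentences, a second item version, a somewhat longer test for patients and a possible practice effect. The article describes the questionnaire as still to be designed, so the change is feasible, and no additional patients are needed.
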